## Abstract

**Background:**

The United Kingdom has one of the highest rates of stillbirth in Europe, resulting in approximately 4,000 stillbirths every year. Potentially modifiable risk factors for late stillbirths are maternal age, obesity and smoking, but the population attributable risk associated with these risk factors is small.

Recently the Auckland Stillbirth Study reported that maternal sleep position was associated with late stillbirth. Women who did not sleep on their left side on the night before the death of the baby had double the risk compared with sleeping on other positions. The population attributable risk was 37%. This novel observation needs to be replicated or refuted.

**Methods/Design:**

Case control study of late singleton stillbirths without congenital abnormality. Controls are women with an ongoing singleton pregnancy, who are randomly selected from participating maternity units booking list of pregnant women, they are allocated a gestation for interview based on the distribution of gestations of stillbirths from the previous 4 years for the unit. The number of controls selected is proportional to the number of stillbirths that occurred at the hospital over the previous 4 years.

Data collection: Interviewer administered questionnaire and data extracted from medical records. Sample size: 415 cases and 830 controls. This takes into account a 30% non-participation rate, and will detect an OR of 1.5 with a significance level of 0.05 and power of 80% for variables with a prevalence of 57%, such as non-left sleeping position.

Statistical analysis: Mantel-Haenszel odds ratios and unconditional logistic regression to adjust for potential confounders.

**Discussion:**

The hypotheses to be tested here are important, biologically plausible and amenable to a public health intervention. Although this case–control study cannot prove causation, there is a striking parallel with research relating to sudden infant death syndrome, where case–control studies identified prone sleeping position as a major modifiable risk factor. Subsequently mothers were advised to sleep babies prone (“Back to Sleep” campaign), which resulted in a dramatic drop in SIDS. This study will provide robust evidence to help determine whether such a public health intervention should be considered.

**Trial registration number:**

NCT02025530

## Background

The death of an unborn child is a tragic public health problem which currently affects approximately 2.6 million families annually worldwide [1]. Unlike other avoidable causes of maternal and child death the rate of decline of late stillbirth (at or over 28 weeks gestation) in high income countries (HICs) has slowed in recent decades [1].

The United Kingdom has one of the highest rates of stillbirth in Europe, ranking 33^rd^ out of 35 high-income countries [1]. The last report from the Centre for Maternal and Child Enquiries (CMACE) highlights a slow decline in the stillbirth rate in the UK from 5.4 per 1000 total births in 2000 to 5.2 per 1000 total births in 2009, [2]. This decline in stillbirth rate is supported by Gardosi [3] who attributes the reduction to the uptake of accredited training in fetal growth assessment. The Lancet Stillbirth Series [1,3,4] has highlighted the silent but prevalent public health problem of stillbirth and together with the UK Stillbirth and Neonatal Death Charity (Sands) and the Royal College of Obstetricians and Gynaecologists (RCOG) has called for research to address these unacceptably high rates.

### Established risk factors for late stillbirth

Current established risk factors for late stillbirth in high income countries are well documented and have largely been identified from population-level epidemiological studies [5]. These include: advanced maternal age (>35 years) [6], obesity [7], smoking [8], reduced antenatal care attendance [9], low socio-economic status [9], women from black and minority ethnic groups [2], reduced fetal movements (RFM) [10] and small for gestational age (SGA) infants [11]. A meta-analysis of population-based studies found the three most important modifiable risk factors for stillbirth were: obesity (population attributable risk (PAR) 8-18%), advanced maternal age (population attributable risk 6-8%) and smoking (population attributable risk 4-7%) [5]. Of these, only cigarette smoking can realistically be addressed by women during pregnancy. Currently in the UK, there are efforts to address increased identification [3] and subsequent management of SGA infants and mothers following presentation with RFM through the implementation of guidelines [12,13]. To date there has been limited research investigating novel, modifiable factors which have the potential to advance knowledge and address important gaps in the field of stillbirth research.

### Novel modifiable factors and late stillbirth

Although adults spend about a third of their lives asleep there had not been any studies that examined a potential relationship between maternal sleep practices and risk of late stillbirth prior to The Auckland Stillbirth Study [14]. This reported that women who did not go to sleep on their left side on the night before experiencing a late stillbirth, had a two-fold increase in risk compared with those who did go to sleep on their left [14]. This effect persisted after adjustment for confounders such as obesity. The PAR for non-left sleep position in this study was 37%, greater than the PARs of obesity, advanced maternal age and smoking combined [4]. In addition, women who got up to the toilet once or less on the last night before the stillbirth, compared to those who got up more often, were also at higher risk of late stillbirth, as were those who regularly slept during the day in the last month, compared to those who did not.

The Auckland Stillbirth Study also asked women about fetal activity preceding stillbirth. In common with previous studies [15,16], a two-fold increase in late stillbirth was reported in women perceiving reduced fetal movements (RFM) [17]. Although, maternal perception of reduced fetal activity is often used to highlight pregnancies that require further investigation [18], the RCOG guideline on the management of RFM highlighted the need for further studies to understand how maternal perception of reduced fetal activity can be used in stillbirth prevention [12]. Another novel finding of Stacey et al. was the association between a single episode of vigorous fetal activity and late stillbirth [17].

In support of the findings of Stacey et al. The Sydney Stillbirth Study recruited 295 women from eight hospitals around Australia; found that women who slept on their backs were four times more likely to have a stillbirth [19]. A small survey of maternal sleep practices in Ghana also identified supine sleeping position with an increased risk of stillbirth (stillbirth rate (3/19) 15.8% in those sleeping supine and (6/197) 3.0% in those in non-supine position; odds ratio (OR) 8.0; 95% CI 1.5-43.2) [20]. However, both these studies were underpowered to identify right sided sleep position as a risk factor and were unable to examine whether or not sleep position was a particular risk-factor for already compromised babies (FGR and RFM). The proposed study will address these issues in an ethnically and socially diverse population.

### Unanswered questions from the Auckland Stillbirth Study

Publication of the Auckland Stillbirth Study and related correspondence in 2011 was accompanied by an editorial by Chappell and Smith which raised several questions [21]; the first concerned reporting bias; specifically those higher educated women would have greater access and uptake of knowledge about sleep position. This seems unlikely as this was the first published report of the association between stillbirth and sleep position. They also raised the issue of reverse causality. The association between longer sleep and not getting up at night might reflect RFM, an indication of a compromised baby, and this compromise reflects the cause of stillbirth, not duration of sleep duration or not rising at night [21]. In subsequent correspondence Frøen et al. also raised the possibility that the study findings are due to confounding by FGR or RFM [22]. They argued that in cases of FGR the smaller uterus might result in a reduction in the normal preference for a lateral sleeping position in late pregnancy, less bladder compression (not having to get up to the toilet as frequently), and thus better and longer sleep duration. In their reply, the Auckland Stillbirth Study team undertook additional analyses adjusting for these factors and the associations between maternal sleep practices and stillbirth did not change.

There was general agreement that before intervention studies can be planned further observational studies are necessary to confirm or refute the findings of the Auckland Stillbirth Study and investigate potential underlying mechanisms. Here, we propose a study which will achieve this in an ethnically and socially diverse population where the effects of FGR and RFM can also be studied.

### Hypotheses

During this study we will test the following hypotheses:

1. Maternal left sided sleep position reduces the risk of late stillbirth.

2. Supine sleep position increases the risk of late stillbirth

3. Increased maternal sleep duration and sleeping during the day increase the risk of late stillbirth.

4. Maternal perception of RFM, prior to fetal death, increases the risk of late stillbirth.

5. Non-left sleep position, in conjunction with prolonged sleep, increases the risk of late stillbirth substantially (that is, there is an interaction between sleep position and prolonged sleep).

6. Non-left sleep position, in conjunction with a compromised baby (for example, FGR, smoke or drug exposure, RFM) increases the risk of late stillbirth.

### Methods/Design

Modifiable risk factors associated with late stillbirth.

### Study design

After due consideration a case control study has been selected as the most appropriate and efficient design, this methodology has been used to study relatively rare disorders such as stillbirth and addresses the aims of this study.

Alternative study designs considered by the study team included a cohort study of pregnant women. However, the size of study required is unfeasibly large; assuming a late stillbirth rate of 3/1,000 births, to identify 291 cases, 97,000 women would need to be recruited at 28 weeks gestation. For a randomised controlled trial (RCT) the requisite sample size would also be prohibitively large. Assuming the absolute stillbirth rate for the non-left sided position is 3.9/1,000 births and the risk is halved by left sided sleeping and that all participants are able to change their sleep position 118,000 pregnant women would be required in each group (power = 80%, p = 0.05). Asking pregnant women who normally sleep on their left to sleep in another position would be unethical as we believe this would increase their risk of stillbirth, thus only women who normally slept on the right or back could be randomised, increasing the sample size by over two fold. Therefore, it is unlikely an adequately powered RCT of individual women will ever be conducted. Importantly, this was also the case for the “back to sleep” campaign for sudden infant death syndrome which was never evaluated by RCT.

### Study setting

Ethical approval has been successfully obtained from Central Manchester Research Ethics Committee (13/NW/0874). Participants will be recruited from a total of 35 maternity units around the Midlands and North of England. The units have been chosen for location irrespective of size or any local demographics. Recruitment to the project and administration of the questionnaire will be carried out locally by research midwives from participating units. These will be supported by three research midwife co-ordinators based in Manchester, Yorkshire and Birmingham.

### Time scale

September 2013 to March 2014: Study set up, obtain ethical and research approval.

April 2014 to December 2015: Recruitment and data collection from all sites.

January 2016 to August 2016: Data analysis, report writing, dissemination of research findings.

### Sample size

If the prevalence of a risk factor in the controls is between 30% and 60% (the prevalence of non-left sleep position in the Auckland Stillbirth Study was 57%) we would need a sample of 291 cases and 582 controls to detect an odds ratio of 1.5 with a significance level of 0.05 and power of 80%. This sample size would also allow us to detect an interaction with an OR of 2.5. The number of women approached to participate in the study needs to be greater than this as we anticipate a proportion of women will not participate in the study, in the Auckland Stillbirth Study this was 28%. Assuming 30% non-participation rate we need to approach 415 eligible cases and 830 eligible controls.

From the data collected during the recruitment of participating units there are approximately 170 normally formed singleton stillbirths in the Greater Manchester region per year, 90 in the Mersey region, 190 in Yorkshire and 160 in the West Midlands this would give an potential annual recruitment of 610 cases. Due to the unpredictability of stillbirth occurrence we have allowed 18–24 months for recruitment.

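### With 291 cases and 582 controls, 80% power for an odds ratio of 1.5 holds at control prevalences of about 40–50%, not throughout the stated 30–60% range, and is slightly missed at 57%

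*Protocol article*

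**What the plan says.** The Sample size section of the protocol article opens with a condition on exposure prevalence, "If the prevalence of a risk factor in the controls is between 30% and 60" (per cent), and then says that "we would need a sample of 291 cases and 582 controls to detect an odds ratio of 1.5 with a significance level of 0.05" and 80% power. In brackets it gives the value for the main exposure: "the prevalence of non-left sleep position in the Auckland Stillbirth Study was 57" (per cent).

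The abstract, under Methods/Design, attaches the same claim to that single value: "power of 80% for variables with a prevalence of 57%, such as non-left sleeping position".

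The recruitment target is built on these numbers: "Assuming 30% non-participation rate we need to approach 415 eligible cases and 830 eligible controls". The article states neither the sample-size formula nor whether the 0.05 is one- or two-sided.

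**The concern.** For a fixed odds ratio, the number of cases needed depends on exposure prevalence. It is lowest somewhat below 50% and rises towards both ends. One figure offered for the whole of 30–60% must therefore meet the requirement at the least favourable point in that range. The figure of 291 looks instead like the requirement near the most favourable point, and 57% is not near it.

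At stake is how a reader interprets the results. The study aims to confirm or refute the sleep-position association reported by the Auckland Stillbirth Study, so an inconclusive odds ratio will be judged against the advertised 80% power for 1.5. The same statement will be applied to any other exposure with a prevalence between 30% and 60%. The 415/830 approach target also carries the 291/582 forward.

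**Working it through.** **Inputs.** From the Sample size section: 291 cases, 582 controls (ratio 1:2), odds ratio 1.5, significance level 0.05, power 80%, control prevalence p0 from 30% to 60%, and 57% for non-left position. Assumption: 0.05 is two-sided, so z = 1.960 for significance and 0.842 for power.

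**Exposure in cases.** p1 = 1.5·p0 / (1 + 0.5·p0), and d = p1 − p0.

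**Formulas for the number of cases n, with 2n controls.**
- Unpooled: n = (1.960 + 0.842)² · [p1(1−p1) + p0(1−p0)/2] / d²
- Pooled: n = {1.960·√[1.5·p̄(1−p̄)] + 0.842·√[p1(1−p1) + p0(1−p0)/2]}² / d², where p̄ = (p1 + 2·p0)/3
- Wald on the log odds ratio: n = (1.960 + 0.842)² · [1/(p1(1−p1)) + 1/(2·p0(1−p0))] / (ln 1.5)²

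**Reproducing the plan's figure.** At p0 = 40%, p1 = 0.60/1.20 = 0.50 and d = 0.10. The unpooled formula gives 7.849 × (0.25 + 0.12)/0.01 = 290.4, so 291 cases and 582 controls. The Wald formula also gives 291 and the pooled formula 290. The stated figure therefore corresponds to a prevalence of about 40%.

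**At 57%.** p1 = 0.855/1.285 = 0.6654, d = 0.09537, p1(1−p1) = 0.2227 and p0(1−p0)/2 = 0.12255.
- Unpooled: 7.849 × 0.3452/0.009095 = 297.9, so 298 cases.
- Pooled, with p̄ = 0.6018: (1.1751 + 0.4945)²/0.009095 = 306.5, so 307 cases.
- Wald: 7.849 × (4.491 + 2.040)/0.1644 = 311.8, so 312 cases.

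**Across the range.** Cases needed for 80% power, with the power that 291/582 gives in brackets:

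| p0 | p1 | Pooled | Unpooled | Wald |
|---|---|---|---|---|
| 30% | 0.3913 | 316 (76.8%) | 324 (75.8%) | 315 (76.9%) |
| 40% | 0.5000 | 290 (80.2%) | 291 (80.1%) | 291 (80.1%) |
| 50% | 0.6000 | 292 (80.0%) | 287 (80.6%) | 295 (79.5%) |
| 55% | 0.6471 | 301 (78.7%) | 294 (79.7%) | 306 (78.1%) |
| 57% | 0.6654 | 307 (77.9%) | 298 (79.1%) | 312 (77.2%) |
| 60% | 0.6923 | 318 (76.5%) | 307 (77.9%) | 324 (75.7%) |

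Exact enumeration of the Pearson chi-square test agrees with the pooled column: 76.8% at 30%, 78.0% at 57% and 76.6% at 60%. A continuity correction raises the requirement further, to about 332, 323 and 334 cases at 30%, 57% and 60%.

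**Detectable odds ratio.** With 291/582, the odds ratio giving 80% power by the pooled formula is 1.52 at 30%, 1.52 at 57% and 1.53 at 60%.

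**Could 0.05 be one-sided?** That would need 249, 242 and 250 cases at 30%, 57% and 60%, and 291 cases would then give about 85–86% power. It does not reproduce 291, and the article does not say it.

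**Inflation for non-participation.** 291/0.7 = 415.7 and 582/0.7 = 831.4, against the stated 415 and 830. This step is consistent apart from rounding down.

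**The case against.** The strongest reply concerns the 57% value. The article names no formula, which is normal in a condensed article. With the unpooled formula the shortfall at 57% is 7 cases (298 against 291), or 0.9 of a percentage point. It is also not explicit that 57% is a control prevalence. If it were the prevalence over cases and controls together, p0 would be about 54%: p1 = 0.81/1.27 = 0.638, and (0.638 + 2 × 0.54)/3 = 0.573. The unpooled requirement there is 291.5 cases, essentially the stated figure. The opening condition makes controls the natural reading, but the alternative cannot be excluded.

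The practical effect is also small. A detectable odds ratio of 1.52 rather than 1.50 would change few interpretations, the effect to be replicated is about two-fold, and the article expects a potential 610 cases a year.

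Most of this stands, and it sets the size of the point. It does not rescue the range: at 30% and 60% none of the three two-sided formulas gives 291, and the unpooled formula, kindest at 57%, is the least favourable of the three at 30%. It also does not bring power at a 57% control prevalence up to 80% under any of them.

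**Conclusion.** The claim of 80% power for all control prevalences from 30% to 60% is too broad. With a two-sided 0.05 level, two controls per case and no continuity correction, 291/582 gives 80% for prevalences of about 40–50%, about 77–79% at 57%, and about 76–78% at 30% and 60%. At 57% the miss is 1–3 points and its size depends on the formula; at the ends it is 2–4 points.

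Three stronger readings are tempting, and the article does not support them:
- A reader might infer that the power claim fails everywhere in the range. It does not: the figure is right near 40–50%.
- A reader might infer that the study is materially underpowered for non-left position. A shift in the detectable odds ratio from 1.50 to about 1.52 does not show that.
- A reader might infer a specific further loss from the adjustment for gestation, hospital and other confounders in the Analysis section. The figures here are unadjusted, and the article gives no unit sizes, exposure variation or confounder strengths from which such a loss could be calculated.

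**What to change.** In the Sample size section and the abstract, say that 291 cases and 582 controls give 80% power for an odds ratio of 1.5 at control prevalences of about 40–50%, about 77–79% at 57%, and about 76–78% at 30% and 60%. Equivalently, give the odds ratio detectable with 80% power as about 1.52 at 57% and 1.53 at 60%. Name the formula and the sidedness, and then quote the single values that formula gives.

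The cost is a few words and a slightly less favourable power figure; recruitment need not change. If the sponsor would rather keep the 80% claim for the whole range, the pooled formula needs 318 cases and 636 controls. At 30% non-participation that means approaching 318/0.7 ≈ 455 cases and 636/0.7 ≈ 909 controls, which is 40 and 79 more than planned.

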### Inclusion criteria

#### Cases

Women with singleton pregnancies ending in late stillbirth (with no congenital abnormality) will be recruited from participating maternity units (n ~ 35) in the Midlands and North of England led by four centre’s in Liverpool, Manchester, Yorkshire and Birmingham.

#### Controls

The control group are women with an ongoing pregnancy at a group matched gestation. Women who subsequently deliver an infant with a congenital abnormality will be excluded from the study analysis. This method for control selection overcomes the limitations of previous studies which used gestation matched live birth cohorts which includes many infants who have risk factors for preterm birth.

### Exclusion criteria

Women with the following criteria will not be eligible for participation in the study:

● Fetus known to have a significant congenital anomaly (as defined by the NHS fetal anomaly screening programme (FASP) – Anencephaly, Open spina bifida, Cleft lip, Diaphragmatic hernia, Gastroschisis, Exomphalos, Serious cardiac abnormalities, Bilateral renal agenesis, Lethal skeletal dysplasia, Edward’s syndrome (trisomy 18), Patau’s syndrome (trisomy 13). http://fetalanomaly.screening.nhs.uk/fetalanomalyresource/whats-in-the-hexagons1/about-the-scan/about-the-11-key-conditions)

● Multiple pregnancy

● Maternal age <16 years

● Women unable to give informed consent.

### Participant recruitment

Prior to their discharge from their maternity unit, eligible women who have had a stillbirth (cases) will be given a brief written description of the study by their midwife or doctor and asked whether a research midwife could contact them to discuss the study. If they agree, a research midwife will contact the woman and explain the study in more detail. If the woman consents to participate, a time and place for the interview will be arranged. Interviews will be conducted by trained research midwives. The co-ordinating midwives based in Manchester, Yorkshire and Birmingham will be responsible for training local research midwives in the structured interview format and in providing an appropriate interview environment. This link will also facilitate ongoing support for local research midwives. A similar recruitment system was established through the Auckland Stillbirth Study where formal feedback from participants was positive and no negative feedback was received regarding recruitment [23]. The investigators already have experience of recruiting parents for studies after stillbirth, which will ensure potential distress is minimised. Rather than being reluctant to participate, bereaved parents are keen to participate in research, even that closely related to their time of loss [24]. We will examine the views of women regarding their participation in this research project in a small nested cohort qualitative study.

Controls will be recruited using a group matching technique, based on the previous four years birth and stillbirth figures, they will be randomly selected from the participating hospitals booking list of pregnant women (Figure 1). The control participants will be approached by their community midwife or research midwife, who will give a brief explanation of the study. If women agree to participate, a time and place for the interview will be arranged. As for the cases we will examine the views of women in the control group regarding their participation in this research project in a small qualitative nested cohort study – this will particularly focus on the impact of recruiting women with an apparently healthy pregnancy to a study about stillbirth.

